### Primary endpoint

Tachysystole.

### Secondary endpoints

Vaginal delivery within 24 h of induction; uterine hyperstimulation; Cesarean section; maternal preference regarding the route of administration of the drug; severe neonatal morbidity (convulsions and neonatal asphyxia) or perinatal death; severe maternal morbidity (uterine rupture, sepsis or admission to the intensive care unit) or maternal death; need for oxytocin; number of doses of misoprostol required to trigger labor; time between the first dose and the beginning of labor and delivery; failed induction; need for epidural anesthesia; operative vaginal delivery; maternal side effects (nausea, vomiting, diarrhea, postpartum hemorrhage and fever); meconium in the amniotic fluid; non-reassuring fetal heart rate; 1st and 5th minute Apgar scores < 7; admission of the newborn infant to the neonatal intensive care unit; and need for neonatal resuscitation.

### Randomization and preparation of the medications

The Random Allocation software program, version 1.0.0 (Isfahan, Iran) will be used to randomize participants in the study to labor induction with sublingual or vaginal misoprostol, using the letters A and B, with no prior knowledge or indication of what each letter means. The meaning of the letters will be defined in a random draw conducted by the pharmacist. Neither the investigators nor the statistician will have access to that information. The pharmacist responsible for preparing the medication will place the sublingual misoprostol tablets + the placebo vaginal tablets or the placebo sublingual tablets + the misoprostol vaginal tablets in standardized boxes in accordance with the randomization list. Everyone else in the study (investigators, statistician and participants) will remain blinded to this information until data analysis is complete.

Identical boxes will be prepared and numbered sequentially from 1 to 140 in accordance with the randomization table. Each box will contain a set of eight vaginal tablets (placebo or 25 μg of misoprostol) and eight sublingual tablets (placebo or 12.5 μg of misoprostol), thus guaranteeing the triple-blind design of the study, since neither the investigators nor the pregnant women nor the statistician will be aware of the contents of the boxes.

The vaginal and sublingual placebo and misoprostol tablets will be produced by the pharmaceutical company *Hebron Indústrias Químicas e Farmacêuticas*. The vaginal tablets of misoprostol consist of misoprostol, together with lactose, microcrystalline cellulose, aerosil, explocel, sorbitol and talc, and are sold commercially under the brand name Prostokos^®^ (25 μg). For the purposes of the present study, the aforementioned pharmaceutical company will prepare 12.5-μg tablets of misoprostol for sublingual use. The placebo vaginal and sublingual tablets will be identical in shape, size, color, smell, taste and weight to those containing the active drug prepared specifically for the study, and will be stored in indistinguishable cardboard boxes.

**Fig. 1 Fig1:**
[figure not shown]
Flowchart of procedures for participant selection and monitoring (CONSORT) [12]

### Analysis

The statistical analysis will be conducted using the Epi Info statistical software program, version 7 (Centers for Disease Control and Prevention, Atlanta, USA), with the groups being identified only as A and B. The identification of the groups will only be revealed once the results have been obtained and tables have been prepared. The categorical variables will be compared in contingency tables using the chi-square test of association and Fisher’s exact test, as pertinent. Risk ratios will be calculated as measures of relative risk, together with their respective 95% confidence intervals. The number needed to treat (NNT) to measure the clinical benefit or harm of the treatments will be calculated, together with their respective 95% confidence intervals.

In relation to the continuous quantitative variables with dissimilar variances, if distribution is normal, the groups will be compared using Student’s t-test for non-paired samples (parametric tests). If distribution is found not to be normal, the Mann-Whitney non-parametric test will be used. These tests will be used to identify specific differences between the two groups.

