**Methods:**

A triple-blind, multicenter, placebo-controlled, randomized clinical trial will be conducted in Brazil at the *Instituto de Medicina Integral [name]* and at the Assis Chateaubriand Maternity Teaching Hospital of the Federal University of Ceará. A total of 140 patients with full-term pregnancies, a live fetus, a Bishop score ≤ 6 and a recommendation of induction of labor will be randomized to one of two groups. One group will receive 12.5-μg sublingual tablets of misoprostol and placebo vaginal tablets, while the other group will receive placebo sublingual tablets and vaginal tablets containing 25 μg of misoprostol. The principal endpoint is the rate of tachysystole. The secondary endpoints are vaginal delivery within 24 h of induction, uterine hyperstimulation, Cesarean section, severe neonatal morbidity or perinatal death, severe maternal morbidity or maternal death, and maternal preference regarding the route of administration of the drug. Student’s t-test, and the chi-square test of association or Fisher’s exact test, as appropriate, will be used in the data analysis. Risk ratios and their respective 95% confidence intervals will be calculated.

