### Inclusion criteria

Gestational age ≥ 37 weeks; live fetus; cephalic vertex presentation; Bishop score ≤ 6; and the presence of clinically satisfactory fetal vitality.

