### Sample size

Predicting a frequency of tachysystole of 6,7% % in the 12.5-μg sublingual misoprostol group (pilot study) and of 13.2% in the 25-μg vaginal misoprostol group [7], for a 95% confidence interval and a power of 80%, 70 women would have to be recruited to each group.

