## Discussion

The technological progress achieved in modern obstetrics permits effective techniques to be used to diagnose maternal and fetal situations requiring early elective delivery. One of the principal limiting factors to this process is the condition of unfavorable cervix, which hampers induction of labor, consequently contributing towards increasing Cesarean section rates.

Misoprostol has been identified as a safe, inexpensive, easily administered option for the induction of labor, with satisfactory results. An experimental study showed that sublingual misoprostol at a dose of 25 μg appears to be effective and is associated with greater maternal satisfaction when used to induce labor in women with an unfavorable cervix. Nevertheless, the rate of tachysystole remains high; therefore, further studies need to be conducted to determine the dose and the ideal time interval between doses to minimize the side effects. The only clinical trial conducted using a 12.5-μg dose of misoprostol administered sublingually, a non-randomized open study with no control group, reported that labor was successfully triggered in 90% of cases, with vaginal deliveries occurring in 60% of the women, and a rate of 47% of vaginal deliveries within 24 h [11]. When the frequency of tachysystole found in that study is compared with others in which misoprostol was used vaginally at a dose of 25 μg, a similar frequency of between 4.3 and 6.6% is found [10]. The systematic review available in the Cochrane Library suggests a global rate of uterine hyperstimulation with no changes in fetal heart rate of 11% with 25 μg of misoprostol, even higher than that found in an earlier review [7]. Nevertheless, these results are based on a single clinical trial with no control group, thus rendering comparisons difficult.

We believe that with this low dose of misoprostol administered sublingually the frequency of tachysystole or uterine hyperstimulation may be lower than that found with the habitual 25 μg dose of misoprostol administered vaginally, since it was suggested in a systematic review that the occurrence of tachysystole with misoprostol is probably dose-dependent [11].

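### Only unadjusted comparisons are planned, so precision available from entry Bishop score and hospital is lost for the common effectiveness outcomes (not for tachysystole)

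*Protocol article*

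**What the plan says.** For categorical outcomes the Analysis section states: "The categorical variables will be compared in contingency tables using the chi-square test of association and Fisher’s exact test, as pertinent". Risk ratios and NNT with 95% confidence intervals accompany these tests. Continuous outcomes get an unpaired t-test or a Mann-Whitney test. Every comparison described is a plain two-group one.

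Two baseline facts are available for each woman. Bishop score is an entry criterion (6 or below, Inclusion criteria), and the trial runs at two hospitals (Setting and recruitment). The Discussion names as a limiting factor "the condition of unfavorable cervix, which hampers induction of labor, consequently contributing towards increasing Cesarean section rates".

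On allocation, the Randomization section says: "Identical boxes will be prepared and numbered sequentially from 1 to 140 in accordance with the randomization table". It does not say whether the list is blocked or stratified, or how the boxes are shared between the hospitals.

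On the primary endpoint, the abstract says: "The principal endpoint is the rate of tachysystole".

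**The concern.** The stated objective covers effectiveness as well as safety. The effectiveness part rests on secondary outcomes: vaginal delivery within 24 h, Cesarean section and failed induction. By the article's own account, the state of the cervix bears on whether induction succeeds and on Cesarean section. All women with a score of 6 or below are nevertheless pooled, and that information is not used. In a trial of 140 women the intervals for these outcomes will be wide, so a baseline variable that is already recorded is worth using.

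The stake is efficiency: wider intervals than necessary for the effectiveness outcomes, and chance differences in cervical status or hospital left in the point estimates.

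**Working it through.** **Inputs from the article.** 70 women per arm; tachysystole 6.7% and 13.2% (Sample size). From the open study of the 12.5-μg dose cited in the Discussion: vaginal delivery within 24 h 47%, vaginal delivery 60%, labor triggered 90%.

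**Inputs assumed.** The article gives no prognostic strengths. For vaginal delivery within 24 h: Bishop odds ratio 1.5–2.5 per SD, centre odds ratio 1–3, two centres of equal size. For tachysystole the Bishop range is widened down to 1.2.

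**The plan's own figure.** The article states "for a 95% confidence interval and a power of 80%, 70 women would have to be recruited to each group". With p1 = 0.067, p2 = 0.132 and mean 0.0995:

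n = [1.96 √(2 × 0.0995 × 0.9005) + 0.842 √(0.067 × 0.933 + 0.132 × 0.868)]² / 0.065² ≈ 332 per arm.

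The stated 70 is not reproduced; 70 per arm gives about 25% power (two-sided 5%). That is a separate problem. It enters here only as the starting point for what adjustment could add.

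**Tachysystole.** Expected events: 70 × 0.067 + 70 × 0.132 = 4.7 + 9.2 ≈ 14. Over the assumed range, Bishop score and centre together explain 0.3% to 10% of the outcome variance. By N/(1 − R²), 140 women act like 140 to 156, and power moves from 24.8% to about 25–27%. Simulated power (20,000 replicates per setting):

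| Bishop OR per SD, centre OR | Crude | Centre-stratified (CMH) | Adjusted for both |
|---|---|---|---|
| 1, 1 | 24.7% | 24.1% | 24.2% |
| 1.5, 2 | 25.8% | 25.1% | 25.3% |
| 2, 2 | 25.7% | 25.1% | 25.4% |
| 2.5, 3 | 25.0% | 24.9% | 26.1% |

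Stratifying by centre gains nothing, and full adjustment gains about one point at the extreme. Type I error of the crude test was 4.6–5.0%.

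**A 47% outcome.** By the same variance-explained formula R² is 4–19%, equivalent to 146–173 women. That is optimistic for a risk ratio. Direct simulation of modified Poisson regression with robust errors gave a variance reduction for the log risk ratio of about 0–17%, with type I error near 5%. A repeat with 6,000 replicates per setting gave 2–15%, inside that range.

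In terms of the interval, with 47% in both arms:

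- Crude SE of the log risk ratio = √(2 × 0.53 / (0.47 × 70)) = 0.179, so the 95% CI around a ratio of 1 is 0.70 to 1.42.
- At the best case, SE = 0.179 × √(1 − 0.17) = 0.164, so the CI is 0.73 to 1.38. This equals 140 / 0.83 ≈ 169 women.
- At the worst case there is no change.

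**Which other outcomes are common enough.** If the cited study's rates held in both arms, up to 40% of 140 = 56 women would not deliver vaginally, so Cesarean section can carry two covariates. Failed induction at 100 − 90 = 10% gives about 14 events, which is thin. Hence the condition on event numbers below.

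**The case against.** The strongest reply is that this is a condensed article. The full protocol and any SAP are not shown, and adjustment for covariates or centre is commonly settled there. The crude comparison is also valid under randomisation: its confidence interval already allows for chance imbalance. Both points stand. What remains is that the article does not merely leave the method open. It states an unadjusted one for every outcome, and that choice can be improved with data already in hand.

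A second reply is that the Discussion speaks of an unfavorable cervix, not of Bishop score, and gives no gradient among the women enrolled. It also says nothing linking cervical status to tachysystole. This stands too, and it is why the gain is shown from zero upwards.

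Three stronger readings are tempting and not supported.

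- A reader might infer from the single 1-to-140 numbering that allocation is unbalanced between hospitals. The article is silent on blocking and stratification, and sequential numbering is compatible with blocks or with a number range for each hospital.
- A reader might infer that chance imbalance invalidates the crude results. If each hospital had 70 women (not stated) and the list were unstratified, a 29:41 split or worse would have probability 6.3%. With a centre odds ratio of 2, that split would shift a 47% outcome by about 2.9 points against a standard error of 8.4, and tachysystole by about 1.0 point against 5.1. These shifts are within what the interval covers.
- A reader might hope that adjustment offsets the small sample for the primary endpoint. The power table rules this out.

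**Conclusion.** The concern holds as an efficiency point limited to the common effectiveness outcomes. The planned analysis is unadjusted throughout, although a baseline variable that the article itself treats as bearing on induction and Cesarean section is recorded for every woman. For an outcome near 47% the loss is about 0–17% of the variance of the log risk ratio. That range depends wholly on the assumed Bishop and centre odds ratios, and on a 47% rate taken from an uncontrolled study. For tachysystole there is essentially no loss. The crude tests are not wrong, and nothing here shows a fault in the randomisation list.

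**What to change.** Before the A/B code is broken, add to the analysis plan:

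1. For vaginal delivery within 24 h and Cesarean section, a risk ratio with 95% CI adjusted for entry Bishop score and hospital. Use modified Poisson regression with robust errors, or Mantel-Haenszel with strata fixed in advance. The regression needs no Bishop cut-point, and the article gives none.
2. The same for failed induction, if the number of events allows.
3. The crude tables, risk ratios and NNT retained for all outcomes.
4. For tachysystole, the crude analysis retained as primary, with at most a supportive Mantel-Haenszel risk ratio stratified by hospital.

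It would also help to state whether the list is stratified or blocked by hospital. If it is, a hospital term follows from the design. No change to the allocation or to the boxes is called for.

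Cost: slightly more analysis and no new data. Because the groups stay coded until the tables are prepared, this can be specified blind. The downside is that the gain may be small if Bishop score is only weakly prognostic among women scoring 6 or below.

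### The Analysis section ties Student's t-test to variables with dissimilar variances, the case in which its equal-variance assumption fails: wrong as written, minor in effect

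*Protocol article*

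**What the plan says.** The protocol article, Analysis section, gives one decision rule, in relation to "continuous quantitative variables with dissimilar variances, if distribution is normal, the groups will be compared using Student’s t-test", in its unpaired form. The other branch depends only on the shape of the distribution: "If distribution is found not to be normal, the Mann-Whitney non-parametric test will be used". The section says nothing of normally distributed variables whose variances are similar, and no unequal-variance version of the t-test is named anywhere in the article.

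The Abstract (Methods) is more general: "Student’s t-test, and the chi-square test of association or Fisher’s exact test, as appropriate, will be used in the data analysis". It attaches no variance condition to the t-test.

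The primary endpoint is a proportion: "The principal endpoint is the rate of tachysystole". Among the secondary endpoints, the quantitative ones are "number of doses of misoprostol required to trigger labor" and "time between the first dose and the beginning of labor and delivery".

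**The concern.** The standard unpaired Student's t-test estimates one common variance from both groups. That is valid when the two population variances are equal. A rule that sends variables to this test because their variances differ reverses the usual logic; the matching method for that case is the unequal-variance (Welch) t-test. An article may leave detail to an analysis plan, but this is a stated rule that is wrong as it reads, not a missing detail.

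What is at stake is the type I error of the comparisons sent down this branch. When the groups are of unequal size, the pooled standard error is too small if the smaller group is the more variable, and too large if the larger group is. The p-value can therefore err in either direction, and the error cannot be excused as conservative.

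**Working it through.** The plan gives no figure for this point, so there is none to reproduce. The check asks how far the pooled test departs from 5% in groups of plausible size.

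**Inputs**
- Planned size: 70 per group (Sample size section).
- Labor triggered in 90% of cases in the earlier uncontrolled 12.5-μg study (Discussion): 0.90 × 70 = 63. Time to labor has no value for a woman who never labors, so 63 v 70 is an extreme case in which every woman in the other group labors.
- Vaginal delivery in 60% in the same study (Discussion): 0.60 × 70 = 42. The comparison figure of 56 (80% of 70) is an assumption.
- SD ratio: not given. Assumed to be 2, with 1.5 and 3 as the range.

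**Formulas** (normal data, no true difference, two-sided 5%)
- Variance of the difference that the pooled test uses, on average: V_pool = [(n₁−1)σ₁² + (n₂−1)σ₂²] / (n₁+n₂−2) × (1/n₁ + 1/n₂)
- True variance: V_true = σ₁²/n₁ + σ₂²/n₂
- Approximate type I error: 2 × [1 − Φ(1.96 × √(V_pool/V_true))]

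**SD ratio 2**
- 70 v 70: V_pool = (69×4 + 69)/138 × 2/70 = 0.0714; V_true = 4/70 + 1/70 = 0.0714. The ratio is 1, so the error is 5.0%.
- 63 (SD 2) v 70 (SD 1): V_pool = 317/131 × 0.03016 = 0.0730; V_true = 4/63 + 1/70 = 0.0778; 1.96 × 0.969 = 1.90, so about 5.8%.
- 63 (SD 1) v 70 (SD 2): V_pool = 338/131 × 0.03016 = 0.0778; V_true = 1/63 + 4/70 = 0.0730; 1.96 × 1.032 = 2.02, so about 4.3%.
- 42 (SD 2) v 56 (SD 1): V_pool = 219/96 × 0.04167 = 0.0951; V_true = 4/42 + 1/56 = 0.1131; 1.96 × 0.917 = 1.80, so about 7.2%.
- 42 (SD 1) v 56 (SD 2): V_pool = 261/96 × 0.04167 = 0.1133; V_true = 1/42 + 4/56 = 0.0952; 1.96 × 1.091 = 2.14, so about 3.3%.

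**Simulation of both tests** (at least 100,000 normal datasets per cell)

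| Groups | More variable group | SD ratio | Student (pooled) | Welch |
|---|---|---|---|---|
| 70 v 70 | either | 1.5 / 2 / 3 | 5.1% / 5.0% / 5.1% | 5.0% / 4.9% / 5.0% |
| 63 v 70 | smaller | 1.5 / 2 / 3 | 5.5% / 5.9% / 6.1% | 5.0% / 5.0% / 5.0% |
| 63 v 70 | larger | 1.5 / 2 / 3 | 4.6% / 4.4% / 4.2% | 5.0% / 5.1% / 5.0% |
| 42 v 56 | smaller | 1.5 / 2 / 3 | 6.4% / 7.3% / 8.3% | 5.0% / 5.0% / 5.0% |
| 42 v 56 | larger | 1.5 / 2 / 3 | 3.9% / 3.3% / 2.9% | 5.0% / 5.0% / 4.9% |

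The simulation agrees with the formula to within about 0.1 percentage point at SD ratio 2. With equal SDs and unequal groups (60 v 80), both tests gave 4.9%, so Welch's test also keeps its level when the variances are in fact equal.

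**The case against.** The strongest reply is that this is a one-word slip with almost no reach. The Abstract names Student's t-test without condition, which suggests it was meant for normal data generally, or for similar variances. That is plausible, but it does not rescue the sentence. If the word should be its opposite, the rule in print is the reverse of the rule intended, and the unequal-variance case is then left without a test.

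The reply on reach largely stands. Nearly all the endpoints are binary. The number of doses is a count of at most eight, and the times are shaped by six-hourly dosing with an overnight pause, so these variables may well be judged non-normal and go to Mann-Whitney. The disputed branch may govern few endpoints or none.

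Three stronger readings are tempting, and the article does not support them:
- A reader might infer that the article names no test at all for similar variances. That is true only of the Analysis section taken alone; the Abstract's general mention covers the case.
- A reader might infer that the Abstract repeats the error. It does not, since it states no variance condition. It is the contrast to the Analysis section, not a second place of the error.
- A reader might infer a material distortion from the 42 v 56 case. That case needs an assumed 56, an assumed SD ratio and an endpoint limited to vaginal deliveries. The Secondary endpoints section lists time to delivery without that limit.

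**Conclusion.** Wrong as written, minor in severity. The Analysis section pairs an equal-variance test with unequal variances and needs correcting whether or not the wording is a slip.

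The primary comparison is not touched. For the quantitative secondary endpoints there is no loss of error control with 70 women analysed in each group. With the group size implied by the article's own 90% labor rate, the pooled test stays within about one percentage point of 5% at SD ratios up to 2, and slightly beyond that at 3 (4.2% to 6.1%). The wider range of about 3% to 7% at 42 v 56 is an illustration that depends on assumptions the article does not make. All these figures assume normal data.

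**What to change.** Replace the sentence pair in the Analysis section with: *Approximately normal continuous variables will be compared with the unequal-variance (Welch) t-test, whatever the sample variances; other continuous variables with the Mann-Whitney test.* The t-test named in the Abstract should be read, or reworded, to match.

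This settles both readings of the present text, because the choice of test no longer depends on a variance check. Tying Student's t-test to similar variances and Welch's to dissimilar ones would also cure the stated error, but would keep that extra step. The cost is one sentence. No new data are needed, the sample size does not change, and the change can be made while the groups are still coded A and B.

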## Discussion

The technological progress achieved in modern obstetrics permits effective techniques to be used to diagnose maternal and fetal situations requiring early elective delivery. One of the principal limiting factors to this process is the condition of unfavorable cervix, which hampers induction of labor, consequently contributing towards increasing Cesarean section rates.

Misoprostol has been identified as a safe, inexpensive, easily administered option for the induction of labor, with satisfactory results. An experimental study showed that sublingual misoprostol at a dose of 25 μg appears to be effective and is associated with greater maternal satisfaction when used to induce labor in women with an unfavorable cervix. Nevertheless, the rate of tachysystole remains high; therefore, further studies need to be conducted to determine the dose and the ideal time interval between doses to minimize the side effects. The only clinical trial conducted using a 12.5-μg dose of misoprostol administered sublingually, a non-randomized open study with no control group, reported that labor was successfully triggered in 90% of cases, with vaginal deliveries occurring in 60% of the women, and a rate of 47% of vaginal deliveries within 24 h [11]. When the frequency of tachysystole found in that study is compared with others in which misoprostol was used vaginally at a dose of 25 μg, a similar frequency of between 4.3 and 6.6% is found [10]. The systematic review available in the Cochrane Library suggests a global rate of uterine hyperstimulation with no changes in fetal heart rate of 11% with 25 μg of misoprostol, even higher than that found in an earlier review [7]. Nevertheless, these results are based on a single clinical trial with no control group, thus rendering comparisons difficult.

We believe that with this low dose of misoprostol administered sublingually the frequency of tachysystole or uterine hyperstimulation may be lower than that found with the habitual 25 μg dose of misoprostol administered vaginally, since it was suggested in a systematic review that the occurrence of tachysystole with misoprostol is probably dose-dependent [11].

This will be the first randomized, controlled clinical trial to compare the effectiveness and safety of misoprostol at a dose of 12.5 μg administered sublingually with the currently standard 25 μg dose administered vaginally every six hours to induce labor in pregnant women with a full-term live fetus. Expectations are that the present study will clarify whether the rate of tachysystole during labor induction is lower in the sublingual group. On the other hand, no differences between the groups are expected with respect to uterine rupture, need for analgesia during labor, need for operative vaginal delivery or the rate of maternal death.

